### Visit schedule

Patients will attend a baseline visit and 6 monthly follow-up visits. The follow-up visits will be scheduled every 30 ± 3 days. If a patient does not complete a follow-up visit within the scheduled period for any reason, we will not collect follow-up data for that time period, and the data for that visit will be considered missing. Patients who fail to attend three consecutive follow-up visits within the scheduled time frame will be excluded from the study. At the baseline visit, we will collect information about demographics, comorbidities, medication history, anthropometric measurements (blood pressure, heart rate, height, and weight), and QoL and hypertensive symptom scales. At each follow-up visit, we will record blood pressure, heart rate, new-onset disease or disease progression, treatment and expenses for the month, and AE data. As a basis for patient compliance judgment and subgroup analysis, we will also record the details of HSM, including the actual dosage, frequency, acupoints, and heat-sensitized sensations at each follow-up visit. QoL and hypertensive symptoms will be assessed at the 3- and 6-month follow-ups. The detailed visit schedule is presented in Fig. 2.

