### Outcomes

#### Primary outcome

The primary outcome is a change in mean SBP (mmHg) at month 6, which will be measured using a uniform Omron upper-arm electronic blood pressure monitor at each study site. The measurement will be performed when the patient is in a resting state.

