### Statistical analysis

Data analysis of the primary outcome will be based on the full analysis set constructed by the intention-to-treat principle, whereby patients will remain in their original group regardless of contamination. The per-protocol set will also be analyzed by sensitivity analysis for the primary outcome to evaluate whether contamination impacts the direction of the effect. The secondary outcomes will also be compared based on the per-protocol set. The need to impute missing values will be determined by the proportion of and reasons for missing data. If imputation is necessary, appropriate methods, such as the last observation carried forward, “best-worst-case” scenario and multiple imputation regression modeling, will be chosen according to the distribution of the missing values.

Data analysis will be conducted separately for the randomized and nonrandomized groups, and consistency of effect directions between the two sets of analyses will be evaluated. For the randomized groups, repeated-measures analysis of variance will be employed for the continuous variables measured each month; QoL and symptom scale scores will be compared by *t* tests, and categorical variables will be compared by chi-square tests. These analyses will not be adjusted for covariates unless there are factors that are significantly unbalanced at baseline. For nonrandomized groups, we will utilize repeated-measures ANOVA, linear mixed models, and logistic regression models depending on the data distribution; potential confounders will be adjusted for, including age, body mass index (BMI), baseline SBP, duration of hypertension, type of antihypertensive regimen, diabetes, dyslipidemia, smoking, and alcohol consumption. The between-group difference will be measured by the mean differences for continuous outcomes (i.e., changes in SBP, DBP, dosage of antihypertensive drug, QoL, and hypertensive symptom scores) and the risk ratios (RRs) for binary outcomes (i.e., the response to treatment and incidence of new-onset cardiovascular events).

We are also interested in whether there are different blood pressure lowering effects between HSM regimens with different parameters, which will be explored by the following subgroup analyses with prespecified effect directions based on our clinical experience:

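### The visit-window and three-missed-visits rules make obtainable month-6 blood pressure missing and leave it unclear whether the excluded patients stay in the intention-to-treat set

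*Protocol article*

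**What the plan says.** Two rules stand in the Visit schedule section of the protocol article. The first concerns single visits. The timing is fixed: "The follow-up visits will be scheduled every 30 ± 3 days". If a visit is not completed in that window, whatever the reason, "we will not collect follow-up data for that time period, and the data for that visit will be considered missing". The second concerns repeated misses: "Patients who fail to attend three consecutive follow-up visits within the scheduled time frame will be excluded from the study".

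The Primary outcome section ties the endpoint to one of these visits: "The primary outcome is a change in mean SBP (mmHg) at month 6".

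The Statistical analysis section then states: "Data analysis of the primary outcome will be based on the full analysis set constructed by the intention-to-treat principle". It explains the principle by saying that "patients will remain in their original group regardless of contamination". On missing data it says: "The need to impute missing values will be determined by the proportion of and reasons for missing data". If imputation is judged necessary, it lists last observation carried forward, a best-worst-case scenario and multiple imputation. For the randomized groups, "repeated-measures analysis of variance will be employed for the continuous variables measured each month".

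No section provides for keeping a reading taken outside the window, for measuring excluded patients at month 6, or for their place in the full analysis set.

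**The concern.** A visit window normally labels a reading as on time or late. Here it decides whether the reading exists. On the natural reading of the rule, a patient who comes a day after the final window closes has no primary endpoint, although the patient was not lost. The exclusion rule goes further. A patient who misses months 3, 4 and 5 is out before month 6, even if able to attend then. A patient who keeps every appointment but always arrives four days after the scheduled day yields no follow-up data and is excluded as well.

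Both rules depend on behaviour after randomization. The Allocation section says that patients and physicians cannot be blinded, and the Discussion expects that HSM patients may find the six-month regimen hard to keep up, especially in hot weather. Attendance may therefore be related to arm and to how well treatment is going. What is at stake is the randomized SBP comparison. Treatment, cost and adverse-event data are recorded at the same visits and are exposed to the same rule.

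**Working it through.** **1. The plan's own figure.** Inputs from Sample size estimation: difference 5 mmHg, SD 8 mmHg, two-sided α = 0.05, power 0.80, attrition 20%.

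N = 2 × ((1.960 + 0.842)/5)² × 8² = 40.19 per arm; 40.19/0.80 = 50.23, rounded up to 51. The stated minimum of 51 is reproduced, and this point does not touch it.

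**2. What the exclusion can mean.** The text allows two readings.

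- *Removed from the analysis.* Randomized patients are dropped for post-randomization attendance, which conflicts with a full analysis set built on intention-to-treat.
- *Follow-up stops, patient stays in the set.* There is no formal conflict, but month-6 SBP is missing by rule and has to be imputed or left out.

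Neither gives an intention-to-treat comparison on measured outcomes, and the article does not say which applies.

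**3. Possible bias.** Let the HSM patients with a month-6 reading have mean SBP reduction R. Let a share m of the arm be missing, with mean reduction R − d, and let the control arm be unaffected. The whole-arm mean is (1 − m)R + m(R − d) = R − md, so a complete-case difference overstates the benefit by m × d. The documents give neither m nor d; these values are assumptions:

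| m | d (mmHg) | overstatement (mmHg) |
|---|---|---|
| 10% | 2 | 0.2 |
| 10% | 5 | 0.5 |
| 20% | 2 | 0.4 |
| 20% | 5 | 1.0 |
| 30% | 2 | 0.6 |
| 30% | 5 | 1.5 |

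The design effect is 5 mmHg, so 1.0 mmHg is one fifth of it.

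**4. Power.** The randomized comparison has 60 compulsory plus 20 voluntary patients, 80 per arm. With 20% attrition and an assumed further 10% missing the month-6 window, 80 × 0.8 × 0.9 = 57.6 per arm remain. The standard error is 8 × √(2/57.6) = 1.49, the ratio 5/1.49 = 3.35, and two-sample t-test power is about 91%. With the compulsory arms alone, 60 × 0.8 × 0.9 = 43.2 per arm and power is about 82%, against 86% at 60 × 0.8 = 48. All of these exceed the planned 80%.

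**The case against.** Four points can be made for the plan.

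*The passages do not flatly contradict each other.* The sentence on staying in the original group concerns the arm in which a patient is analysed, and exclusion from the study may mean only that follow-up ends. Imputation is provided for. This stands in part: a reader might infer an outright contradiction, but the text supports only a tension that must be reconciled. Imputation is conditional, however, and does not replace a reading that could have been taken.

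*The article does not describe a patient in the clinic being refused a reading.* The rule might be aimed at filling in a missed month's expenses or HSM frequency afterwards. That is possible, but the wording covers all follow-up data for the visit and makes no exception for blood pressure.

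*Power is not at risk.* This stands. A reader might infer a serious loss as follows: if 10% of visits miss the window independently, 1 − 0.9⁶ = 47% of patients have at least one void reading, and a complete-case repeated-measures analysis would keep 60 × 0.9⁶ = 31.9 per compulsory arm, with power of about 69%. The documents do not support that. They do not specify complete-case deletion, they leave imputation open, and they randomize 80 per arm; 80 × 0.9⁶ = 42.5 gives about 81% on the same assumptions. Misses clustered within patients would also lower the 47%.

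*Bias is not shown.* This also stands. Missing patients need not do worse, and losses in the control arm could offset those in the HSM arm.

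**Conclusion.** The point holds in a limited form. As written, the two rules create avoidable missing values at the primary time point, nothing else in the article repairs this, and a later analysis plan cannot recover readings that sites were told not to take. The status of excluded patients in the full analysis set is unresolved.

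Bias in the SBP comparison is plausible, given the open-label design and the expected adherence difficulty in one arm, but neither its size nor its direction is known. The 1.0 mmHg illustration rests on assumed m = 20% and d = 5 mmHg, missingness in the HSM arm only, and a complete-case analysis. It would be wrong to conclude that the rules certainly bias the result or leave the trial underpowered. The reason to act is the integrity of the primary endpoint, which a larger sample would not restore.

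**What to change.** Amend the Visit schedule section for all visits still to come.

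1. Record SBP and the other outcomes, with the actual date, whenever the patient attends. Keep ±3 days as a target and as the definition for a sensitivity analysis. If two readings map to the same month, use the one closest to the scheduled day.
2. Replace the exclusion after three missed visits with a statement that these patients stay in the full analysis set, and that a month-6 SBP is sought for every randomized patient whatever the earlier attendance.

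The cost is changed protocol and case report form wording, a brief instruction to sites, and slightly more spread in measurement dates. Trial status gives recruitment from 10 March 2021 and an expected finish in June 2022. Readings already not taken cannot be recovered, and earlier and later visits will have been collected under different rules, so the report should state the date of the change.

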**Fig. 2 Fig2:**
[figure not shown]
Schedule of study visits

### Data collection and management

At each study site (i.e., community healthcare center), a community physician will be responsible for patient recruitment, HSM training, and outcome assessment; a clinical coordinator will be responsible for regular contact with patients with regard to follow-up visits, recording basic information, and distributing moxibustion materials. Prior to the start of the trial, all investigators will be trained on the standard operating procedure and complete simulated baseline and follow-up visits before being allowed to conduct the investigation.

Raw data will be recorded on paper-based case report forms stored in a lockbox at each study site. Electronic data entry will be performed at any interim analysis and at the end of follow-up by an approach in which two clinical coordinators independently and repeatedly enter the data into standardized forms created in Microsoft Access (Microsoft Corporation, USA). The electronic data set will be anonymized and kept confidential. Only the blinded data analyst can access the data set.

The following trial committees will be established for quality assurance: a steering committee consisting of acupuncturists, cardiologists, methodologists, and statisticians and responsible for study design, maintenance of the quality of study conduct, safety monitoring, and study publication; a coordinating center consisting of the principal coordinating investigator and the coordinating investigators of each community and responsible for the overall study conduct, interactions with the communities and sponsors, and reporting trial advancements to the steering committee; an independent endpoint adjudication committee consisting of cardiologists and acupuncturists and responsible for reviewing the assessment of the primary endpoint and subjective outcomes; and an independent data-monitoring committee consisting of acupuncturists, cardiologists, methodologists, and statisticians for monitoring the data management, directing the interim analysis, and deciding whether to continue the trial based on the results of safety, efficacy, and compliance assessment.

### Recruitment and compliance enhancement

Patients will be invited to participate in the study by their primary care physician at each site. The recruitment advertisement will also be disseminated through posters and the internet. A full understanding of the 6-month follow-up schedule and signing of the informed consent form are prerequisites for participation. Patients’ long-term trust in their physicians is an essential guarantee of their willingness to participate in the study and comply with the protocol. At each visit, patients will obtain a comprehensive health assessment and recommendations for adjusting their medications for hypertension and other diseases. We will also provide a number of rooms with air conditioning and fume extractors at each study site for the patients to administer HSM.

To promote recruitment and compliance, we will provide the patients in both the randomized and nonrandomized HSM groups with two boxes of moxa rolls (108 rolls) per month, which is enough for consumption during the month. At the baseline visit, we will also give the patients two free moxibustion jars, each equipped with a fleece bag that can be slipped over the outside to prevent burns. At the follow-up visits, we will ask the patients to bring the moxibustion jars with them to determine whether the reported frequency of HSM matches the thickness of soot accumulation on the jars. If a moxibustion jar breaks, we will replace it with a new jar. Patients randomized into the control group will receive two more boxes of moxa rolls and two more moxibustion jars than those in the HSM group after completing the study. Because they are not interested in performing HSM, after completing the study, the patients who voluntarily enter the control group will be given a blood pressure monitor that is of equal value to the moxibustion materials.

### Sample size estimation

The primary purpose of sample size estimation is to meet the need for statistical power for primary outcome comparison between randomized groups. Based on the results of our previous nonrandomized studies (not yet published) and expert opinion, we assume that the SBP in the HSM group will be on average 5 mmHg lower than that in the control group after 6 months of HSM treatment, with a common standard deviation of 8 mmHg between the groups. With a type I error probability “α” of 0.05 and type II error probability “β” of 0.20 and the allowance of a 20% attrition rate, a minimum of 51 patients in either the randomized HSM or control group is needed, as calculated by the following formula for the superiority design [22]:
$$ N=2\times {\left(\frac{Z_{1-\frac{\alpha }{2}}+{Z}_{1-\beta }}{\upmu_1-{\upmu}_2}\right)}^2\times {s}^2 $$

We ultimately decided to enlarge the total sample size to 400, as a sample of this size can be supported by funding. We administered a small preference survey to 100 patients at the study sites, which showed that the ratio of patients with a preference (a strong willingness to enter the HSM or control group) to those without a preference (accept the randomization) was approximately 6:1. Considering the feasibility of the study and the need for confounder adjustment, we established a sample size for the voluntary randomization group of 40 (20 per group) such that the size of the preference selection (nonrandomized) group would be 240 (120 per group). The remaining 120 patients will be entered into the compulsory randomization group (60 per group). Figure 1 illustrates the sample size scheme for each arm.

### Statistical analysis

Data analysis of the primary outcome will be based on the full analysis set constructed by the intention-to-treat principle, whereby patients will remain in their original group regardless of contamination. The per-protocol set will also be analyzed by sensitivity analysis for the primary outcome to evaluate whether contamination impacts the direction of the effect. The secondary outcomes will also be compared based on the per-protocol set. The need to impute missing values will be determined by the proportion of and reasons for missing data. If imputation is necessary, appropriate methods, such as the last observation carried forward, “best-worst-case” scenario and multiple imputation regression modeling, will be chosen according to the distribution of the missing values.

Data analysis will be conducted separately for the randomized and nonrandomized groups, and consistency of effect directions between the two sets of analyses will be evaluated. For the randomized groups, repeated-measures analysis of variance will be employed for the continuous variables measured each month; QoL and symptom scale scores will be compared by *t* tests, and categorical variables will be compared by chi-square tests. These analyses will not be adjusted for covariates unless there are factors that are significantly unbalanced at baseline. For nonrandomized groups, we will utilize repeated-measures ANOVA, linear mixed models, and logistic regression models depending on the data distribution; potential confounders will be adjusted for, including age, body mass index (BMI), baseline SBP, duration of hypertension, type of antihypertensive regimen, diabetes, dyslipidemia, smoking, and alcohol consumption. The between-group difference will be measured by the mean differences for continuous outcomes (i.e., changes in SBP, DBP, dosage of antihypertensive drug, QoL, and hypertensive symptom scores) and the risk ratios (RRs) for binary outcomes (i.e., the response to treatment and incidence of new-onset cardiovascular events).

We are also interested in whether there are different blood pressure lowering effects between HSM regimens with different parameters, which will be explored by the following subgroup analyses with prespecified effect directions based on our clinical experience:
A high degree of heat-sensitized sensation is expected to be associated with better efficacy than a low degree. A scale developed in-house will be used to measure the degree of heat-sensitized sensation. The scale includes four dimensions (depth/range/distance [not available for three systemic reactions], intensity, frequency, and comfort) for 12 sensations (Additional file 2). Each dimension can receive a score of 0 to 5 points. A patient whose total score in the four dimensions for any sensation is ≥ 60% (i.e., 15 points) will be considered to have achieved a high degree of heat-sensitized sensation. This scale was tested in a sample of 64 patients and showed good reliability and validity—the Cronbach alpha coefficient was 0.892, and the factor loadings for all items were > 0.6.HSM ≥ 4 times per week is expected to be associated with better efficacy than HSM < 4 times per week.Heat-sensitized sensations at both the main and matching acupoints are expected to be associated with better efficacy than heat-sensitized sensations at only the main acupoint.The development of nonthermal sensation (the last 7 moxibustion sensations on the scale) is expected to be associated with better efficacy than the development of only thermal sensation.

In addition, subgroup analyses comparing patients who underwent compulsory and voluntary randomization will be carried out to validate the impact of patient preference on the effects.

If the HSM group shows a better response to treatment than the control group, we will perform an economic evaluation in which the cost-effectiveness ratio and incremental cost-effectiveness ratio will be used as indicators. If a better response to treatment is associated with the frequency of HSM, the balance between the costs of moxibustion materials and outcomes will be explored. A cost-effectiveness acceptability curve will be applied to visualize information about uncertainty in the cost-effectiveness analysis.

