### Interventions and cointerventions

In the HSM group, patients will self-administer HSM to treat hypertension. At trial entry, physicians will follow a predetermined standard operating procedure to stimulate the patient for heat-sensitized sensations using round-trip meridian, circling, and sparrow-pecking techniques around any of the acupoints at Yongquan (KI1), Shenque (CV8), and Baihui (GV20) as well as Dazhui (GV14), Quchi (LI11), Hegu (LI4), Taichong (LR3), and Zusanli (ST36). The former three are the main acupoints, and the latter four are the matching acupoints. The patients will select one main acupoint and one matching acupoint with the strongest heat-sensitized sensation as acupoints for HSM self-administration. For bilateral matching acupoints (i.e., Quchi, Zusanli, Hegu, and Taichong), the side with the stronger heat-sensitized sensation will be selected. The administration of HSM at the matching acupoint can be abandoned if all fail to stimulate heat-sensitized sensations.

After acupoint selection, the physicians will explain in detail the technique of HSM to the patients or their families, including how to use the moxibustion jar, ignition, and safety precautions (e.g., preventing burns and smoke evacuation). When dose saturation is achieved (i.e., the heat-sensitized sensations disappear), HSM can be stopped, or the patient can wait until the moxa column has burned completely (approximately 30 min). We will recommend that patients administer HSM once per day at home or at a community healthcare center. Driven by the pragmatic design, we will allow for a lower frequency of HSM when patients are busy, but the procedure must be completed at least two times per week.

Patients in both the HSM and control groups will maintain the use of their original antihypertensive regimen, including antihypertensive drugs or no treatment. The study treatments will last 6 months for all patients. During the trial period, all patients will be prohibited from receiving other acupoint stimulation therapies, such as acupuncture, acupressure, transcutaneous electrical stimulation, or acupoint application therapy. Regular treatment for comorbidities, such as glucose-lowering drugs for patients with diabetes and lipid-lowering drugs for those with dyslipidemia, will be allowed.

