## Discussion

Blinding is usually not feasible in RCTs involving healthcare techniques that require manual manipulation [23], including HSM. Consequently, patients will clearly know whether they are receiving the experimental intervention, and patient preference may cause uncertain effects on the study process and results [24, 25]. To reduce patient preference effects, we chose to perform a randomized patient preference trial, from which several advantages can be derived. First, this design allows us to analyze patient-preference effects by comparing the results of compulsory and voluntary randomization. Another benefit of a compulsory randomization group is avoiding being unable to achieve randomization when the proportion of patients who choose voluntary randomization is too small. Second, evaluation of randomized and nonrandomized samples will improve the reliability of the results if they can be corroborated. The evidence from nonrandom samples will also have better external validity. Third, this design will allow the study to recruit more participants, and the patients in the patient preference cluster will be more adherent to the protocol and less likely to be lost to follow-up.

A potential limitation of this study is that the patients in the HSM group may not easily adhere to the 6-month HSM treatment regimen, especially when the weather is hot. Although we will provide air-conditioned rooms at each study site for them to administer HSM, there is no guarantee that all patients will be willing to visit during the hot months of the summer. Nevertheless, patient compliance is an important outcome, and poor compliance would suggest that this community-based HSM model is not feasible. In addition, although the hypertensive symptom scale implemented in this study is from an authoritative guideline and has been used in a number of studies [15] to date, there is no direct evidence to support its reliability and validity.

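### Secondary outcomes are assigned only to a per-protocol set, so the randomized comparisons of response, dosage, events and cost-effectiveness may be exposed to selection bias of unknown size and direction

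*Protocol article*

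**What the plan says.** Three consecutive statements in the Statistical analysis section of the protocol article settle the analysis sets.

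- Primary outcome, main analysis: "Data analysis of the primary outcome will be based on the full analysis set constructed by the intention-to-treat principle".
- Primary outcome, second analysis: "The per-protocol set will also be analyzed by sensitivity analysis for the primary outcome to evaluate whether contamination impacts the direction of the effect".
- Secondary outcomes: "The secondary outcomes will also be compared based on the per-protocol set".

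The Secondary outcomes section lists DBP, response to treatment, antihypertensive dosage, QoL, symptom severity, new cardiovascular events, HSM compliance and cost-effectiveness. Adverse events are a separate category and are not assigned to the per-protocol set.

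The article gives no criteria for the per-protocol set. Rules that could become criteria are found elsewhere. Under Interventions and cointerventions, HSM may be done less often than daily, but "the procedure must be completed at least two times per week". The same section says that "all patients will be prohibited from receiving other acupoint stimulation therapies". The Visit schedule section removes patients who miss three consecutive visits. In the Discussion the authors foresee that "the patients in the HSM group may not easily adhere to the 6-month HSM treatment regimen".

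**The concern.** In a superiority trial, randomization protects a comparison only while patients are analysed as assigned. A per-protocol set is formed by what patients do afterwards, and in an open-label add-on trial the two arms are asked to do different things. The HSM arm has a procedure to carry out several times a week for six months. For the controls, "Patients in both the HSM and control groups will maintain the use of their original antihypertensive regimen, including antihypertensive drugs or no treatment", and no matching use threshold is stated. Differences between the retained groups can then reflect who was retained as well as what HSM does.

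Several secondary outcomes carry real weight. Dosage answers one of the questions posed in the Background, whether HSM can replace some drug doses. A better response in the HSM group is the condition for running the economic evaluation, and the response rate is the denominator of the cost-effectiveness ratio. The Discussion says that poor compliance would mean the community model is not feasible. If compliance were judged only in patients retained because they complied, that signal would be lost. The trial is also described as pragmatic, so the question is what happens in the community population, not among those who followed the protocol.

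**Working it through.** **The plan's own figure.** The point rests on no stated number, but the sample size shows which comparison was planned for. Inputs from Sample size estimation: difference 5 mmHg, SD 8 mmHg, two-sided α 0.05, power 0.80, attrition 20%.

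N = 2 × ((1.960 + 0.842)/5)² × 8² = 40.19 per arm; 40.19/0.8 = 50.23, rounded up to 51. The stated 51 is reproduced. It concerns SBP only. The planned randomized arms hold 60 + 20 = 80 patients each.

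**Reading the assignment.** The full-analysis-set sentence names the primary outcome and nothing else. The secondary-outcome sentence names the per-protocol set and nothing else. Nothing in the article states a full-analysis-set comparison for any secondary outcome.

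**Which rules could remove whom, if used as criteria.**

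| Rule | HSM arm | Control arm |
|---|---|---|
| At least two HSM sessions per week | yes | cannot apply |
| No other acupoint therapies | yes | yes |
| Three consecutive missed visits | yes | yes |
| Contamination | possible | yes, by taking up HSM |

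The last three can act in both arms, though not necessarily equally. Only the first is one-sided, and its use as a criterion is an inference.

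**Illustration of possible bias.** The documents give no non-adherence rate and no outcome gap between adherent and non-adherent patients. Everything here is assumed: true response 40% in both arms (no effect), 80 per arm, a fraction f of the HSM arm excluded, no controls excluded, and the excluded patients' response rate lower by d than that of the retained.

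Retained HSM response = 0.40 + f × d; risk ratio = (0.40 + f × d)/0.40. The type I error is that of a two-sided 5% test by normal approximation, with 80(1 − f) HSM patients against 80 controls.

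| f | d | Retained HSM response | Risk ratio | Type I error |
|---|---|---|---|---|
| 10% | 10 points | 41% | 1.03 | 0.052 |
| 20% | 20 points | 44% | 1.10 | 0.077 |
| 30% | 30 points | 49% | 1.23 | 0.181 |

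For a continuous outcome the false difference is f times the gap. With f = 20% and a gap of 0.5 SD it is 0.10 SD (type I error 0.092); with f = 30% and 1 SD it is 0.30 SD (0.406).

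**The same arithmetic in other directions.**

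- If the excluded HSM patients have the same prognosis as the retained (d = 0), the risk ratio is 1.00.
- If they would have done better by 20 points at f = 20%, retained response is 0.40 − 0.04 = 0.36 and the risk ratio is 0.36/0.40 = 0.90.
- If instead 20% of controls are removed and those removed do worse by 20 points, retained control response is 0.44 and the risk ratio is 0.40/0.44 = 0.91.
- If f and d are equal in both arms, the shifts cancel.

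On the full analysis set the expected null risk ratio is 1.00 and the type I error 0.05, apart from missing data. No sample size changes.

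**The case against.** The strongest reply is that the sentence contains the word *also*. The sentence before it uses that word for a per-protocol analysis done in addition to the main one, so the authors may have meant both sets for the secondary outcomes too. That reading is possible. Even so, no full-analysis-set comparison of secondary outcomes is stated, and nothing says which set governs. The same edit resolves both readings.

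A second reply is that per-protocol criteria belong in the analysis plan, which is not shown. That stands: the missing definition is not the complaint. The choice of set is stated in the article, and it is a weakness whatever the criteria turn out to be, because removing contaminated controls also departs from the randomized groups.

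A reader might infer more: that the twice-weekly rule is a per-protocol criterion, that the patients it removes have a poorer prognosis, and that every secondary comparison is thereby tilted towards HSM. The documents do not support this. The rule is an instruction on the intervention and is never tied to the set; the only purpose given for the set is to look at contamination. The reasons mentioned for low use are being busy and hot weather, neither of which indicates prognosis. Other rules can remove controls. Compliance has no control comparison to tilt, and dropping low users could raise the apparent cost of HSM.

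Two further replies limit the reach. The primary outcome, the only one the sample size addresses, keeps intention to treat with per-protocol as sensitivity. And 240 of the 400 patients are nonrandomized, so the lost protection concerns the 160 randomized patients.

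**Conclusion.** The concern holds in a limited form. As written, the plan compares the secondary outcomes on a per-protocol set and commits to no intention-to-treat comparison for them. For the randomized arms this gives up the protection of randomization for DBP, response, dosage, QoL, symptoms, cardiovascular events and cost-effectiveness. These results may be exposed to selection bias; it cannot be said from the documents that they are biased, by how much, or in favour of which arm.

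The range of 1.03 to 1.23 for the response risk ratio shows what one-sided exclusion could do with no true effect. It rests wholly on assumed exclusion fractions, response gaps and a 40% response rate, with no control exclusions, and is not a forecast. The circularity of the compliance result likewise depends on compliance being a criterion for the set. The primary analysis is unaffected.

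**What to change.** Replace the sentence on secondary outcomes with: *Secondary outcomes, including cardiovascular events and cost-effectiveness, will be compared on the full analysis set; the per-protocol set is a sensitivity analysis for primary and secondary outcomes.* Add that HSM compliance will be reported for all patients assigned to HSM.

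The cost is a sentence or two of analysis wording. No new data, patients or sample-size revision are needed. The price the authors may notice is that estimates can look less favourable than those from patients who followed the protocol; the per-protocol results remain available alongside.
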